### Interventions and measurements

Baseline values for QoR-15 and pain Numeric Rating Scale (NRS) are collected before the day of surgery. On the day of surgery, preoperative preparations on the ward follow local routines. A standardised premedication with acetaminophen and ondansetron is recommended. On arrival in the operating room all subjects are provided with basal monitoring including Bispectral Index (BIS). Induction and maintenance of anaesthesia is performed primarily with propofol and remifentanil or sevoflurane and fentanyl. Intubation and ventilator settings are managed according to local routine. Propofol or sevoflurane administration is controlled primarily by BIS, while the administration of remifentanil or other opioids intraoperatively is governed primarily by subject haemodynamics.

Haemodynamic treatment with fluids and drugs is performed according to local routine. A dose of 0.07 mg/kg actual body weight (ABW) intravenous morphine is recommended 30–60 min before the planned awakening, as well as 1 mcg/kg ABW intravenous fentanyl at the termination of remifentanil infusion when used.

Subjects randomised to the intervention group receive preoperative spinal analgesia with 15±5 mg bupivacaine and 0.2–0.3 mg conservative-free morphine using a 24G or smaller spinal pencil-point needle. In case of difficult puncture and/or pronounced discomfort, the procedure is aborted, and the subject is treated with intravenous lidocaine similar to the control group.

In subjects randomised to the control group, an intravenous infusion of lidocaine is started as soon as possible after induction. A bolus dose of 2 mg/kg ideal body weight (IBW, corresponding to a body mass index (BMI) of 22 kg/m^2^) is given over 10 minutes. An infusion of 2 mg/kg/hour IBW is then started. In patients with a BMI <22, ABW is used for calculation of bolus and maintenance doses. The infusion is terminated at the end of surgery or earlier in the event of unexplained severe hypotension or severe arrhythmias.

Additional intraoperative use of local anaesthetics, for example, for infiltration of trocar ports, is not allowed, with the exception of wound infiltration in case of unplanned conversion to laparotomy in patients in the morphine spinal group. Paracetamol 1 g is administered intravenously or orally every 6 hours to all patients. The addition of other adjuvant analgesics, such as NSAIDs, gabapentin, COX-2 inhibitors, clonidine and magnesium, is not permitted intraoperatively. Postoperatively, opiates and adjuvant analgesics are administered at the discretion of the responsible nurse or physician according to local routines. This includes the use of patient-controlled analgesia devices and the transition from intravenous to oral opioids. The use and doses of intraoperative and postoperative opioids and adjuvant analgesics are recorded on the day of surgery and postoperative day (POD) 1. To allow comparison of opioid doses between the groups, administered opioid doses are converted into morphine equivalents. Also, on POD 7, the use of opioid analgesics after discharge is recorded.

After surgery, the patient is transferred to the PACU (post-anaesthesia care unit). Registration of pain at rest and during movement is performed 2±0.5 hours after arrival at the PACU. Treatment of pain and nausea follows local routines. When local PACU discharge criteria are met, the patients is transferred to the ward where treatment is given according to local routine.

The subject fills in a diary 3 times a day during the first 3 PODs in the hospital or at home, recording pain at rest and during movement, and other indices of recovery. The second QoR-15 is registered by trial staff 24±2 hours after the end of anaesthesia. On POD 7, trial staff call the subject and record the third QoR-15 and obtain information about pain, pruritus, bowel function and postoperative opioid use. If the subject is still hospitalised, data are collected by telephone or on site. Any postoperative complications and length of stay are recorded based on a review of the subject’s record that takes place between POD 31 and 44.

#### Haemodynamics/inflammation subgroup

In a subgroup of 50 patients having surgery at US Linköping, additional haemodynamic measurements will be performed. On arrival at the anaesthesia department, an arterial line is placed and connected to a pulse-contour analysis device (Pulsioflex, Getinge, Gothenburg, Sweden). Mean arterial pressure, cardiac index, stroke volume index, heart rate, stroke volume variation, pulse pressure variation, systemic vascular resistance index, cardiac power index and dPmx (measure of contractility of the heart's left ventricle) are recorded and stored continuously 5 times per min. In addition, the above measurements are recorded manually on a separate sheet on arrival at the operating room, just before anaesthesia, before the start of surgery, 1 hour after the start of surgery, at the end of surgery, on arrival at the PACU and on discharge from the PACU.

In the same subgroup, blood is sampled for analysing the inflammatory and neuroendocrine response on the day of surgery before arriving in the OR, 1 hour after abdominal insufflation, 2 hours after the end of anaesthesia and on POD 1 and 3 (if not discharged). A study flow chart is shown in figure 1.

**Figure 1 F1:**
[figure not shown]
Study flow chart. NRS, Numeric Rating Scale; PACU, post-anaesthesia care unit; POD, postoperative day; PRE, preoperative; QoR, Quality-of-Recovery; US, University Hospital Linköping.

### Outcome measures

Primary and secondary outcome measures of this study are shown in table 2 with additional details provided in online supplemental table 1. The primary outcome measure of this study is QoR-15 on POD 1. Our primary hypothesis is that the reduction in QoR-15 from baseline before surgery to POD 1 is at least 8 points less in the morphine spinal group compared with the control group treated with intravenous lidocaine.

**Table 2 T2:** Primary and secondary outcome measures

**1**	**QoR-15 score at POD 1 (primary outcome measure)**
2	QoR-15 score preoperatively
3	QoR-15 score at POD 7
4	Pain (NRS) at rest and during motion 2 hours after arrival to the PACU
5	Pain (NRS) on POD 1–3
6	Pain (NRS) at rest and during motion on POD 7
7	Time from arrival in the OR to start of surgery
8	Time from end of surgery until leaving the OR
9	Incidence of unplanned termination of the lidocaine infusion
10	Amount of remifentanil in patients given remifentanil
11	Amount of intraoperative opioids in patients not receiving remifentanil, expressed in morphine equivalents
12	Length of stay at the PACU/ICU/HDU
13	Amount of opioids administered at the PACU/ICU/HDU during the first 24 hours after end of surgery
14	PONV requiring treatment at 0–6 hours and 6–24 hours postoperatively as well as during the whole postoperative stay
15	‘Time out-of-bed’ on POD 1–3
16	Amount of opioids administered during the first 24 hours at the PACU/ICU/HDU and in the ward
17	First POD passing gases
18	First POD passing stool
19	Incidence of pruritus
20	Length of stay
21	DAOH30
22	Postoperative complications until POD 30
23	Requirement for opioids after discharge
24	Incidence of respiratory depression leading to the use of a μ-antagonist within 48 hours of induction of anaesthesia
25	Intraoperative fluid balance
26	Time with low blood pressure during anaesthesia
27	Lowest MAP within 10 min after induction of anaesthesia
28	Highest MAP within 10 min of start of abdominal insufflation
29	Fraction of patients needing norepinephrine within 15 min after start of abdominal insufflation
30	Fraction of patients needing norepinephrine intraoperatively (later than 15 min after start of abdominal insufflation)
31	Average infusion rate of norepinephrine, in patients receiving norepinephrine, before 15 min after start of abdominal insufflation
32	Average infusion rate of norepinephrine, in patients receiving norepinephrine, after 15 min after start of abdominal insufflation
33	Intraoperative Cardiac Index
34	Intraoperative Stroke Volume Index
35	Intraoperative Cardiac Power Index
36	Intraoperative dPmx
37	Intraoperative Pulse Pressure Variation
38	Intraoperative Stroke Volume Variation
39	Intraoperative dynamic arterial elastance
40	Intraoperative Systemic Vascular Resistance Index
41	Intraoperative heart rate
42	Biochemical markers of inflammation

DAOH30, Days alive and out of hospital at postoperative day 30; dPmx, A measure of contractility of the heart's left ventricle; HDU, high dependency unit; ICU, intensive care unit; MAP, mean arterial pressure; NRS, Numeric Rating Scale; OR, operating room; PACU, post-anaesthesia care unit; POD, postoperative day; PONV, postoperative nausea and vomiting; QoR-15, Quality-of-Recovery 15.

### Safety outcome measures

Safety outcome measures that are recorded in this study are presented in box 1.

Box 1Safety outcomesOccurrence of intraoperative or postoperative arrhythmia requiring cardioversion or defibrillation and/or treatment with amiodarone during the stay.Occurrence of intraoperative or postoperative hypotension or bradycardia requiring treatment with adrenaline, epinephrine, isoprenaline and/or vasopressin during the stay.Occurrence of circulatory instability (arrhythmia or hypotension) postoperatively which prompts a transfer to a higher level of care, for example from the PACU to the ICU or from the ward to the CCU or the ICU during the stay.Occurrence of a suspected generalised epileptic seizure intraoperatively or postoperatively during the stay.Occurrence of decreased consciousness which causes a move to a higher level of care, for example, from the PACU to the ICU or from the ward to the CCU or ICU, during the stay.Presence of opioid-induced respiratory depression that has led to treatment with µ-antagonists and/or invasive respiratory therapy during the stay.Occurrence of premature discontinuation of lidocaine infusion.CCU, coronary care unit; ICU, intensive care unit; PACU, post-anaesthesia care unit.

### Adverse events

Adverse events are defined as incidents, adverse medical events or worsening of an existing medical condition in a subject receiving an investigational drug. Screening for adverse events will be performed at fixed point during the trial (figure 1). In addition, adverse events may be reported at any time during the trial. Adverse events will be assessed for their seriousness and possible relation to the study drugs. Some events are deemed to be naturally related to the surgical procedure and are therefore not registered as adverse events in this trial. These events are specified in box 2.

Box 2Events not registered as adverse events in this trialPostoperative pain.Postoperative nausea and/or vomiting.Constipation.Lack of appetite.Infectious diseases not fulfilling Clavien-Dindo criteria for grade 2 or above.Coagulopathy.Pruritus.Renal dysfunction not leading to a specific intervention.Urinary retention.Hypovolaemia and major bleeding related to the surgery.Intraoperative or postoperative arrhythmia not requiring cardioversion and/or defibrillation and/or treatment with amiodarone.Intraoperative or postoperative hypotension or bradycardia not requiring treatment with epinephrine, isoprenaline and/or vasopressin.Transient impact on consciousness in direct connection to the operation that does not lead to a transfer to a higher level of care, for example, from the PACU to the ICU, from the ward unit to the PACU or CCU or ICU.Opioid-induced respiratory depression that does not prompt treatment with a µ-antagonist and/or invasive ventilatory therapy during the stay.Other known complications clearly related to the intraoperative course such as bleeding (including postoperative), crush injuries, pressure neuropathy, vascular damage and ischaemic damage to the limb or face, including eyes and oral cavity.CCU, coronary care unit; ICU, intensive care unit; PACU, post-anaesthesia care unit.

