Due to the disadvantages of morphine spinal, it is clinically relevant to investigate whether morphine spinal is actually better than an alternative additional treatment without the disadvantages of morphine spinal. Of the possible strategies considered to have the potential to approach equivalent effect on postoperative recovery as a morphine spinal, only intravenous lidocaine is not associated with renal effects or a negative effect on tumour progression.

Lidocaine given intravenously perioperatively for pain relief is a so-called ‘off-label’ use, similar to many other drugs used in anaesthesia, for example, epidural fentanyl. The use of lidocaine in this way is currently limited in Sweden, but it is routine in many hospitals abroad and is recommended in various international guidelines.^24 25^ The bolus dose and infusion rate in the current trial are well in line with previous studies on the effect of lidocaine as a pain-relieving drug given intravenously.^13^

The lidocaine infusion will be started and finished while the subject is closely monitored in the operating room. Signs of systemic toxicity will thus be detected early and treatment rapidly initiated. The relatively short treatment time means that the risk of accumulation and late toxicity is considered negligible, even in subjects with pre-existing or new-onset renal failure. The infusion is stopped prematurely if severe unexplained hypotension or arrhythmia occurs. Patients with severe kidney or liver failure or advanced heart disease will not be included in the trial. The use of larger doses of local anaesthetic in other ways during the primary operation is not permitted in those receiving lidocaine.

The trial involves the handling of sensitive personal data. The risk of various forms of privacy infringement is minimised through informed consent and pseudonymised processing and storage of research data, including sample material.

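### Box 2 lets hypotension, bradycardia or arrhythmia that stops the lidocaine infusion, or postoperative hypotension or arrhythmia that sends a patient to higher care, go without seriousness and causality assessment

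*Protocol article*

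**What the plan says.** Under Adverse events, the article states: "Adverse events will be assessed for their seriousness and possible relation to the study drugs". It then removes a list of events from registration (Box 2) on the ground that they belong naturally to the surgery. Three of those items matter here:

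- Hypotension and bradycardia: "Intraoperative or postoperative hypotension or bradycardia not requiring treatment with epinephrine, isoprenaline and/or vasopressin".
- Arrhythmia: "Intraoperative or postoperative arrhythmia not requiring cardioversion and/or defibrillation and/or treatment with amiodarone".
- Consciousness: "Transient impact on consciousness in direct connection to the operation that does not lead to a transfer to a higher level of care".

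Box 1 (Safety outcome measures) includes two outcomes that are defined by a consequence and not by a treatment: "Occurrence of circulatory instability (arrhythmia or hypotension) postoperatively which prompts a transfer to a higher level of care" and "Occurrence of premature discontinuation of lidocaine infusion". The stop of lidocaine is also item 9 of Table 2.

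The stopping rule is given under Interventions and measurements: "The infusion is terminated at the end of surgery or earlier in the event of unexplained severe hypotension or severe arrhythmias". The Ethics section repeats it: "The infusion is stopped prematurely if severe unexplained hypotension or arrhythmia occurs". Neither place sets a drug or cardioversion threshold.

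**The concern.** The two boxes use different triggers for the same kind of event. Box 2 asks which drug or procedure was used. Box 1 asks, for two of its outcomes, whether the patient was moved to higher care or the study infusion was stopped. An event can satisfy Box 1 without reaching any Box 2 threshold, and it is then not registered as an adverse event.

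The events are not lost from the data, because the stop and the transfer are still recorded. What can be lost is the judgement of seriousness and of relation to the study drugs. These are events for which that judgement matters. The Introduction and the Ethics section both name hypotension as an effect of the study spinal. The stopping rule for lidocaine, which is used off-label here, refers to hypotension that has no other explanation. The stated reason for the exemptions, that the events come from the surgery, does not cover either case. The Discussion also presents the trial as a source of further safety data on perioperative lidocaine.

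**Working it through.** The plan gives no figure to reproduce, so the check sets each Box 1 outcome against the matching Box 2 item and asks whether one event can satisfy both.

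| Box 1 safety outcome | Matching Box 2 exemption | Result |
|---|---|---|
| Arrhythmia needing cardioversion, defibrillation or amiodarone | Arrhythmia not needing these | Complementary; registrable |
| Hypotension or bradycardia needing the listed drugs | Same condition not needing them (Box 1 names adrenaline and epinephrine, which are one drug, so the lists agree) | Complementary; registrable |
| Postoperative arrhythmia or hypotension prompting transfer | Both circulatory items, with no transfer exception | **Can be exempt** |
| Suspected generalised seizure | None | Registrable |
| Decreased consciousness prompting transfer | Consciousness item, which excepts transfer | Complementary; registrable |
| Opioid respiratory depression treated with a µ-antagonist or invasive support | Same condition not so treated | Complementary; registrable |
| Premature stop of lidocaine | Both circulatory items, with no exception for a stop | **Can be exempt** when the cause is hypotension, bradycardia or arrhythmia |

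Count: 5 registrable + 2 that can be exempt = 7 Box 1 outcomes. Box 2 has 15 items, and 2 of them create the gap.

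Two cases show how it arises.

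1. **Lidocaine stopped.** A patient in the lidocaine arm develops unexplained severe hypotension. The infusion is stopped, and the pressure is restored with fluids or norepinephrine. The stop is counted in Box 1 and in Table 2 item 9. No drug named in the Box 2 item was used, so the hypotension is exempt.
2. **Transfer.** A patient in either arm has postoperative hypotension and is moved to the ICU on norepinephrine, or has an arrhythmia and is moved to the CCU without cardioversion or amiodarone. The transfer is counted in Box 1. The event is exempt.

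Neither case needs unusual treatment. Norepinephrine is the vasopressor that Table 2 follows (items 29 to 32), and it is not among the drugs that lift the hypotension exemption.

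Patients exposed: case 1 can arise only where lidocaine is given, planned as 220 / 2 = 110 patients plus any spinal-arm patients switched to lidocaine after a failed puncture. Case 2 can arise in all 220. These are the sizes of the groups, not counts of expected events.

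The rest of the article was searched for a rule that overrides Box 2 when an event is serious, prompts transfer or stops study drug. There is none.

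**The case against.** The strongest counter-argument is that the article condenses a fuller protocol. Seriousness criteria and reporting rules usually sit in that document, which may say that any serious event is registered regardless of Box 2. This stands as a limit on certainty. It does not remove the point, because the article sets out the exemptions item by item with explicit thresholds. The mismatch lies between two stated rules and does not depend on something left out.

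A second argument is that stopping lidocaine already requires a clinician to find the hypotension severe and unexplained, and that an unexplained event fits poorly with the reason given for Box 2. The clinician's decision to stop is not, however, a documented assessment of seriousness and causality, and the Box 2 item turns on treatment alone.

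Third, the stop or the transfer is not itself listed in Box 2, and the definition of adverse events is broad enough that either might be registered as an incident. That reading is possible, but the text does not state it, and sites may differ in applying it.

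Fourth, the events reach the data by other routes: Box 1, Table 2, the record review after day 30, the safety board and the annual report to the regulator. This is correct, and it is why the concern is confined to the missing assessment. It is also correct that only part of each of the two outcomes is affected: a stop for seizure, or a transfer in which a listed drug or procedure was used, remains registrable.

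**Conclusion.** The concern holds. As the article is written, two of the seven Box 1 safety outcomes can include circulatory events that Box 2 keeps out of adverse-event registration, and so out of the seriousness and relatedness assessment. The pattern points to an oversight: four other Box 1 outcomes have an exactly complementary Box 2 item, seizure is not exempted at all, and the consciousness item already carries the missing transfer exception.

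The number of events cannot be derived from the article and may be small. The primary outcome, the sample size and the efficacy conclusions are untouched. The conclusion assumes that Box 2 is applied literally and that the full protocol has no override for serious events. On that basis the text should be corrected, though the trial's main result is not at risk.

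**What to change.** Add one clause to each of the two circulatory items in Box 2: the exemption does not apply if the event prompts transfer to a higher level of care, leads to premature termination of the lidocaine infusion, or meets a seriousness criterion. Routine hypotension treated with norepinephrine stays exempt, in line with the Ethics section, which regards such treatment as standard practice. If the full protocol already contains such an override, it is enough to state it beside Box 2.

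Then check the records of patients already included (54 by 1 October 2025) against the corrected list. Start with those who have a Box 1 entry for circulatory transfer or early lidocaine discontinuation.

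The cost is one clause in two items, a few more adverse-event forms and one record check. Treatment and statistical analysis do not change.

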### Statistics

#### Calculation of sample size

In a previous feasibility study including 30 patients undergoing robot-assisted upper urinary tract surgery under general anaesthesia without morphine spinal or intravenous lidocaine, QoR-15 decreased from a median (IQR) preoperative value of 141 (128 – 145) to 106 (88–103) on POD 1 (means (SD) 136 (11) and 105 (22); unpublished data). We assume that variance ((SD)^2^) is 400 in both groups on POD 1. With an MCID of 8, a desired alpha value of <0.05 and a power of 80% 100 subjects are needed in each group (GPower V.3.1.9.7, Heinrich-Heine-Universität Düsseldorf, Germany). To compensate for dropouts, a total of 220 subjects will be included in the trial.

#### Analysis groups

The primary outcome is analysed in the entire trial group according to the intention-to-treat (ITT) principle, except for the subjects who do not undergo the planned robot-assisted surgery within 12 months from inclusion, and/or neither receive intervention nor control treatment, and/or leave the trial and/or die before the POD 1 measurement. The clinical secondary analyses are also analysed in this entire trial group according to ITT. These analyses will be supplemented with:

A per protocol (PP) analysis of the primary hypothesis as well as NRS POD 1–3, where subjects who are included in the ITT analysis, however, without sufficient preoperative effect of the spinal analgesia, and/or where lidocaine infusion was prematurely terminated, and/or where the surgery was converted to an open procedure are excluded.An ITT and PP analysis as above where subjects with problematic pain are omitted. Problematic pain is defined here as preoperative opioid use for more than 1 month.

The haemodynamic and biochemical parameters are analysed only in the subgroup that is monitored with advanced haemodynamic monitoring according to the PP principle, that is, subjects with a spinal anaesthetic without adequate preoperative spread, and/or where lidocaine infusion was prematurely terminated, and/or where the surgery was converted to an open procedure are excluded.

Normal distribution will be tested with the Shapiro-Wilks test, except for QoR-15 and NRS data which are assumed to be not normally distributed. All significance tests are done two-sided. A p value lower than 0.05 is considered significant. No corrections for multiple comparisons are made unless otherwise specified.

Single missing values are in principle not imputed. In exceptional cases, if missing data cause an entire data series (in time) to be misleading, the missing data can be imputed with the average value of the two measurements closest in time, provided that this results in a reasonable value.

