### Protocol adherence

Intervention and comparator groups will receive the treatment only on one occasion (preoperatively and intraoperatively, respectively). An anaesthetist will provide the intrathecal analgesia and anaesthesia staff will administer the intravenous lidocaine. Drug administration is routinely documented in the anaesthesia record as well as in a separate trial drug log.

Study staff will visit the subject in the surgical ward to obtain the QoR-15 on POD 1 (primary outcome). Study staff will try to reach the subject on telephone on POD 7 between 09:00 and 21:00. On that occasion, the subject will also be reminded to send in the diary if not already done. For subjects who withdraw from the study, no additional data will be collected; however, previously collected data will be analysed.

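### The set called ITT drops randomised patients for post-randomisation events and is reused for DAOH30 and 30-day complications, so early deaths vanish from outcomes meant to count them

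*Protocol article*

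**What the plan says.** All references are to the protocol article.

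- **Analysis groups, the claim:** "The primary outcome is analysed in the entire trial group according to the intention-to-treat (ITT) principle".
- **Analysis groups, the exceptions in the same sentence:** "except for the subjects who do not undergo the planned robot-assisted surgery within 12 months from inclusion", and those who "neither receive intervention nor control treatment, and/or leave the trial and/or die before the POD 1 measurement".
- **Analysis groups, secondary outcomes:** "The clinical secondary analyses are also analysed in this entire trial group according to ITT".
- **Outcome measures, Table 2:** the secondary outcomes include item 21, "DAOH30, Days alive and out of hospital at postoperative day 30", and item 22, "Postoperative complications until POD 30".
- **Interventions and measurements:** complications and length of stay are taken from a review of the patient's record between POD 31 and POD 44.
- **Inclusion and randomisation:** patients are randomised after inclusion and before anaesthesia starts.
- **Blinding:** the patient and the anaesthesiologist in charge know the treatment.
- **Protocol adherence:** "For subjects who withdraw from the study, no additional data will be collected; however, previously collected data will be analysed".

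**The concern.** An ITT comparison keeps randomised patients in the arm to which they were allocated, whatever happens next. Here three of the four exclusions (no study treatment received, withdrawal, death) rest on events after randomisation in an open-label trial. Not being treated, or choosing to leave, could therefore depend on the arm, and what remains is no longer protected by randomisation.

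For the POD 1 QoR-15 itself, a patient who has died or left has no score under any label. For DAOH30 and 30-day complications no such reason exists. A death before POD 1 is a known and extreme result on an outcome defined by being alive, yet the rule removes it. A patient who has the operation, stays in the trial but receives neither study treatment can supply every outcome, the primary one included, and is removed as well.

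The withdrawal rule also cannot be followed as written. One section promises to analyse what was collected before withdrawal. The other removes anyone who leaves before the POD 1 measurement from every clinical secondary analysis.

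**Working it through.** **1. The exclusions set against the data that would exist**

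- *Neither treatment received, surgery done:* POD 1 QoR-15, DAOH30 and complications are all obtainable. All are dropped.
- *Death before POD 1:* there is no QoR-15 score, but DAOH30 and complications are determined without one. Both are dropped.
- *Withdrawal before POD 1:* intraoperative data and the 2-hour PACU pain score may already be recorded. They are dropped, against Protocol adherence. Later follow-up is not collected, so full 30-day outcomes may be missing under any set.
- *No planned surgery within 12 months:* the article does not say how long before anaesthesia randomisation takes place, so some of these cases may precede it.

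**2. The plan's own figure**

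Inputs from Calculation of sample size: difference 8, variance 400 (SD 20), alpha 0.05 (two-sided, from Analysis groups), power 80%.

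n per arm = 2 × (1.960 + 0.842)² × 400 / 8² = 98.1, so 99 by the normal approximation. The t-test solution is 99.08, rounded up to 100. The stated 100 per arm is reproduced. The dropout allowance is 220 − 200 = 20, and 20/220 = 9.1%.

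The point does not turn on this figure. Keeping patients costs no power: by the normal approximation, 110 per arm gives 84.3%, against 80.7% at 100.

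**3. Possible size for QoR-15 (assumed inputs)**

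Suppose k of 110 patients are removed from one arm only and would have scored on average d points below those who remain. The arm mean then rises by k × d / 110.

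| k | d = 20 | d = 40 |
|---|---|---|
| 3 | 3 × 20/110 = 0.55 | 3 × 40/110 = 1.09 |
| 5 | 5 × 20/110 = 0.91 | 5 × 40/110 = 1.82 |
| 10 | 10 × 20/110 = 1.82 | 10 × 40/110 = 3.64 |

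Against the 8-point target, k = 3 gives 0.55/8 = 7% to 1.09/8 = 14%.

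A Mann–Whitney simulation used 6,000 runs per setting, normal scores with mean 105 and SD 20, no true effect, and poor recoverers removed from one arm only. The two-sided rejection rates were:

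- no exclusions: 4.7% to 5.2%
- k = 3: 5.4% to 5.5%
- k = 5: 5.8% to 7.0%
- k = 10: 9.5% to 15.2%

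**4. Possible size for DAOH30 (assumed inputs)**

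One death counted as 0 days, against an assumed typical 26 to 28 days: removing it raises the arm mean by 26/110 = 0.24 to 28/110 = 0.25 day.

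**The case against.** The best reply is that the plan is open about its set. The exceptions stand in the same sentence as the label, so no reader is misled. Any workable remedy also conditions on surgery taking place, and so is a modified ITT too. Few exclusions are likely: treatment is given on one occasion, an aborted spinal is switched to lidocaine and kept in its allocated arm, and a prematurely stopped infusion is excluded only from the per-protocol analysis. Emergencies and ASA class 4 or above are excluded at entry, so death within about a day should be rare. Deaths would still be seen through adverse event reporting and the safety board, and the article does not expressly apply the reduced set to the safety outcomes. All of this stands, and it limits the size of the problem. It does not explain why an early death should leave DAOH30, and it does not resolve the conflict over withdrawn patients.

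Four stronger readings might be inferred, and the documents do not support them.

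- **The rule is built to favour one arm.** As written it is symmetric: a patient in either arm who gets neither treatment is excluded. Keeping an aborted spinal as allocated is correct ITT practice. A difference by arm is possible because treatment is open, but nothing shows that it is expected.
- **The bias is about 1.8 points, 23% of the target effect.** That takes a 9.1% loss (10 of 110) in one arm, all 20 points worse, with nothing offsetting in the other arm. It is an extreme case.
- **A missing POD 1 QoR-15 would be filled from baseline and POD 7, far above the postoperative trough.** The default is no imputation. The exception, under which a value may be "imputed with the average value of the two measurements closest in time, provided that this results in a reasonable value", is for exceptional gaps that distort a series in time. Nothing extends it to the single POD 1 score, and it has no bearing on whether a set is ITT. The fair remark is only that its conditions are not defined.
- **The plan lacks multiple imputation and delta-adjusted sensitivity analyses.** These commonly belong in a statistical analysis plan, which is not shown. Mixed-effects models for longitudinal data are already specified.

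**Conclusion.** The point holds as a fault in the stated rules. The set is a modified ITT set under an ITT label. Its use for the clinical secondary outcomes removes early deaths from DAOH30 and 30-day complications without need, and it contradicts the article's own statement on data collected before withdrawal.

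The numerical effect is probably small: about 0.5 to 1.1 points of QoR-15 for three one-sided exclusions that are 20 to 40 points worse, and about 0.25 day of mean DAOH30 per removed death. Both figures rest on assumed counts and scores, since the documents give none. Only around ten exclusions, all in one arm, would clearly disturb the primary test.

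For the primary outcome, what deaths and withdrawals leave open is the label and how a patient without a score is handled. The wording should be corrected; the point does not undermine the trial.

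**What to change.** 1. Define the main set as every randomised patient who has the planned surgery, analysed as allocated whether or not study treatment was received. Call it modified ITT, because it still conditions on surgery. Keep the present narrower set as supportive only.
2. Keep patients who die before POD 1 in DAOH30, as 0 days, and in complications to POD 30.
3. For each secondary outcome, use what was collected before withdrawal, and reword Analysis groups and Protocol adherence so that they agree.
4. For POD 1 QoR-15, add a sensitivity analysis that gives early deaths the worst rank. This fits the planned rank-sum test.
5. State that the neighbour-averaging exception does not apply to POD 1 QoR-15.

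The cost is a change of wording and a little more analysis. No new data and no larger sample are needed. According to Trial status, 54 patients had been included by 1 October 2025, and the first interim analysis comes after 100 operations. At that date the change could still be made before any comparison of the arms.
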